### Outcomes

#### Primary outcome

Total pain experienced over the first 3 days postrandomisation.

Total pain will be calculated using the standardised area under the curve (AUC) approach from seven individual pain scores, measured using a 0–10 Numerical Rating Scale (NRS) (see wording in online supplemental file S2). The first (baseline) pain score is collected in person prerandomisation as part of a participant questionnaire pack. The remaining six scores are collected postrandomisation at approximately 12-hour intervals (around 8 am and 8 pm) via SMS survey (hereby referred to as timepoints 1–6 (T1–T6)). Actual time of response will be recorded. Alternative methods to collect pain scores (in-person, telephone) are available if SMS is not feasible, depending on staff capacity.

Total pain was chosen as the primary outcome after extensive Patient and Public Involvement (PPI) work. Reduction in erythema has previously been used as a cellulitis outcome measure by regulators,^18^ but was not chosen in this trial for multiple reasons. First, patient feedback was that pain and symptoms were much more important than the size of the erythema. Second, measurement of erythema might be biasing against those of skin of colour. Pain was identified as a key issue for patients with cellulitis, aligning with recent priority setting partnerships.^19^

#### Secondary outcomes

For the secondary outcomes, listed below, continuous outcomes will be reported as means and binary/categorical outcomes will be reported as percentages at the specified timepoints.

Health-related quality of life, measured by EuroQol 5 Dimension 5 Level (EQ-5D-5L)^20^ at day 3, day 14 and day 90 postrandomisation.Patient Global Impression of Improvement (PGI-I)^21^ measured daily for first 3 days (via SMS at T2, T4 and T6) and at day 14 postrandomisation.Analgesia usage (number and type of analgesia taken over first 3 days) postrandomisation, collected at day 14.Antibiotic usage (route, type and postrandomisation length of course) up to day 14 postrandomisation.(Re)admissions to hospital by day 14 postrandomisation.Complications of dexamethasone use by day 14 postrandomisation.Unscheduled healthcare usage until day 14 postrandomisation.Health, social care and broader societal resource use, measured by a resource use questionnaire based on the Modular Resource Use core module (ModRUM)^22^ tailored to the study population, to day 90 postrandomisation.Recurrence of cellulitis by day 90 postrandomisation.Serious and/or potentially related adverse events by day 90 postrandomisation.Pain experienced at day 14 postrandomisation, measured using NRS^23^ (0–10).

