### Objectives

*Primary objective:* to establish if the addition of dexamethasone to treat patients presenting to urgent secondary care with cellulitis reduces total pain reported over the first 3 days (postrandomisation) compared with a control (placebo).

*Secondary objectives:* to determine whether the addition of dexamethasone, when compared with a control (placebo), to treat patients with cellulitis presenting to urgent secondary care with cellulitis: (a) improves quality of life and other patient-reported outcomes, (b) reduces subsequent antimicrobial prescribing, analgesia usage and healthcare utilisation and (c) is cost-effective.

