### Statistical methods

A detailed Statistical Analysis Plan (SAP) will be written following Gamble *et al*^26^ guidelines, approved by an independent statistician, and made publicly available before the trial follow-up period concludes. Any amendments to the SAP will be documented. Results will be reported following the CONsolidated Standards Of Reporting Trials (CONSORT) statement and relevant extensions (e.g., for Patient Reported Outcomes, Pragmatic Trials). Emphasis will be on estimation rather than hypothesis testing; tests will be at the 5% two-sided level. Baseline characteristics will be summarised descriptively overall and by allocated group (means/SDs or medians/IQR for continuous; Ns/% for categorical), with no formal between-group testing of baseline data. A CONSORT flow diagram will illustrate participant flow.

The primary analysis population will be all randomised participants who contribute at least two out of a possible seven pain scores, with the second pain score being at least 24 hours after the baseline pain score. The primary outcome (pain AUC, standardised 0–100) will be analysed using a mixed-effects linear regression model, adjusting for baseline pain, age, sex and the minimisation variables (severity of cellulitis (Eron stage^27^ 1 vs all other stages), antimicrobial therapy for this episode prior to attending urgent secondary care, diabetes status) as fixed effects, and recruitment site as a random effect to account for potential between-site heterogeneity. The adjusted difference in means (and 95% CI) between dexamethasone and placebo groups will be reported; unadjusted difference will also be reported. The primary estimand addresses the effect of dexamethasone plus usual care versus placebo plus usual care, with a treatment policy strategy for intercurrent events. Missing pain scores for the primary outcome will be imputed using linear interpolation if scores are available on either side; if final scores are missing, last observation carried forward (a conservative approach) will be used. Sensitivity analyses will explore other imputation methods (e.g., multiple imputation using chained equations including allocated group, baseline score, centre, minimisation variables, age, sex and predictors of missingness). If an imbalance in baseline characteristics thought to be predictive of outcome is noted, the analysis will be repeated adjusting for these.

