Secondary continuous outcomes (PGI-I, pain at 14 days) will be analysed using mixed-effects linear regression models if assumptions are met; PGI-I at days 1, 2 and 3 will use a mixed-effects repeated measures model. Alternative modelling (eg, mixed-effects ordinal logistic models, dichotomisation for logistic regression) will be considered if assumptions are not met, detailed in SAP. Dichotomous secondary outcomes (additional antibiotic use, (re)admission, unscheduled healthcare use, recurrence) will be analysed using mixed-effects logistic models (if event numbers allow). All models will adjust for the same factors as the primary analysis. Adjusted differences in means or ORs (with 95% CIs) will be reported, along with unadjusted estimates.

Descriptive analysis will cover compliance, analgesia details, antibiotic details and dexamethasone-related complications. The estimands framework for secondary outcomes will mirror the primary outcome. Multiple imputation may be considered for missing secondary outcome data. SAEs will be reported descriptively by whether the first dose was taken (not intention to treat (ITT)).

Exploratory subgroup analyses on the primary outcome (not powered for) will be pre-specified for: cellulitis location (lower limb vs other) and NSAID usage at randomisation (user vs non-user). The primary analysis model will be refitted including an interaction term between treatment and the subgroup of interest; minimum numbers for these analyses will be pre-specified in the SAP.

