The chosen dose and duration of dexamethasone (total 16 mg over 24 hours) are relatively low compared with its use in other conditions and are much lower than doses associated with severe adverse effects in other contexts; extensive experience suggests a favourable safety profile for short courses in infection. However, the trial incorporates measures to manage potential risks associated with short-term corticosteroid use (e.g., hyperglycaemia in patients with diabetes and gastrointestinal upset), such as eligibility screening, site training and resources, additional patient information and monitoring (further details are available in online supplemental file S3).

The active involvement of patients and the public (PPI) throughout the trial’s design (e.g., input on outcomes, patient-facing materials, data collection methods) and planned conduct, including specific engagement with underserved groups like people who inject drugs and people with skin of colour, strengthens its relevance and inclusivity.

If this trial demonstrates that adjunctive dexamethasone is effective and safe for treating cellulitis in urgent secondary care settings, it has the potential to change clinical practice for a very common and burdensome condition. This could lead to improved patient outcomes, such as faster pain relief and recovery, and more efficient use of healthcare resources by potentially reducing reconsultations, antibiotic courses and hospital admissions. The findings will be disseminated widely through academic publications, presentations and to patient and public groups and guideline committees to ensure that they reach clinicians, patients and policymakers, thereby facilitating translation into practice.

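### Day-14 complications of dexamethasone, a listed secondary outcome, is assigned descriptive analysis with no stated between-arm estimate or interval, and no objective covers harm

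*Protocol article*

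**What the plan says.** The Secondary outcomes section names two harm outcomes: "Complications of dexamethasone use by day 14 postrandomisation" and "Serious and/or potentially related adverse events by day 90 postrandomisation". It adds that "binary/categorical outcomes will be reported as percentages at the specified timepoints". Table 2 schedules the review of possible dexamethasone complications at the day-14 call for every participant, and the Blinding section keeps participants, clinicians and assessors unaware of allocation.

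The Statistical methods section treats the binary secondary outcomes in two ways. Additional antibiotic use, (re)admission, unscheduled healthcare use and recurrence go into mixed-effects logistic models if there are enough events, with adjusted and unadjusted estimates and 95% confidence intervals. For the harm outcome at day 14 it says: "Descriptive analysis will cover compliance, analgesia details, antibiotic details and dexamethasone-related complications". The same section opens with the principle that "Emphasis will be on estimation rather than hypothesis testing".

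The primary objective is pain over three days. The secondary objectives cover quality of life and other patient-reported outcomes, and then "b) reduces subsequent antimicrobial prescribing, analgesia usage and healthcare utilisation and (c) is cost-effective". Harm appears in neither. The Discussion nevertheless has a sentence that begins: "If this trial demonstrates that adjunctive dexamethasone is effective and safe for treating cellulitis in urgent secondary care settings".

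**The concern.** The day-14 complications outcome is a randomised, blinded comparison in a trial of a corticosteroid given to people with an infection. The Potential harms section itself names severe hyperglycaemia, gastrointestinal bleeding and psychosis as risks that need monitoring in this population. An outcome of that kind calls for an estimate of the difference between arms and a statement of how precise it is.

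If two percentages are printed side by side without an interval, a real excess may be read as similar rates, and a chance excess may be read as harm. A reader weighing a gain in pain, given with an interval, against complications given without one has to supply the missing half. That sits badly with the article's stated preference for estimation, and it leaves any later safety statement without a stated basis. The absence of a harm objective points the same way: the outcome is collected, but no stated question asks for it to be compared.

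The point concerns the day-14 complications outcome only. How serious adverse events are tabulated is a separate matter.

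**Working it through.** **Inputs.** From the Sample size section: difference 10, SD 30, 90% power, two-sided 5%, 191 per group evaluable, 15% loss, 225 per group recruited. The documents give no complication rate, so all risks and event counts below are assumptions.

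**1. The plan's own figure.** Normal approximation: n = 2(1.960 + 1.282)² × 30²/10² = 189.1, so 190 per group. The t-test version gives 190.1, rounded up to 191. With 15% loss, 382/0.85 = 449.4, so 450. The stated sample size reproduces. It addresses pain only; no figure is stated for harm.

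**2. Precision available for complications.** With the same risk p in both arms, the 95% half-width for the risk difference is 1.96 × √[2p(1−p)/n]. For p = 5% and n = 225: 1.96 × √(2 × 0.05 × 0.95/225) = 1.96 × 0.02055 = 4.0 points.

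| Assumed risk | n = 225 per arm | n = 191 per arm |
|---|---|---|
| 1% | ±1.8 | ±2.0 |
| 2% | ±2.6 | ±2.8 |
| 5% | ±4.0 | ±4.4 |
| 10% | ±5.5 | ±6.0 |
| 20% | ±7.4 | ±8.0 |

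The 191 column borrows the 15% loss planned for pain scores as an illustration of day-14 loss. At 1% and 2% only about 2 and 4 events per arm are expected, so the simple formula is rough. Newcombe intervals there, with 225 per arm, are ±2.4 and ±2.9 points.

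**3. What side-by-side percentages would hide.** Newcombe's interval combines the Wilson limits (l, u) of each arm: lower = d − √[(p₁−l₁)² + (u₂−p₂)²], upper = d + √[(u₁−p₁)² + (p₂−l₂)²]. Illustrative counts, 225 per arm:

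- 20 v 11: 8.9% (Wilson 5.8 to 13.3) v 4.9% (2.8 to 8.5); difference 4.0 points, 95% CI −0.8 to 8.9.
- 12 v 5: 5.3% (3.1 to 9.1) v 2.2% (1.0 to 5.1); difference 3.1 points, 95% CI −0.5 to 7.1.

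Neither interval excludes zero, and neither excludes an excess of about 7 points.

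**4. Zero events in an arm.** The exact upper limit (two-sided 95%) is 1 − 0.025^(1/n): 1.6% for n = 225 and 1.9% for n = 191.

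**5. Why an interval and not a test.** Approximate power to detect a doubling is Φ[(Δ − 1.96·SE₀)/SE₁], with SE₀ from the pooled risk and SE₁ from the separate risks. For 5% v 10% and n = 225: (0.05 − 1.96 × 0.02483)/0.02472 = 0.054, so 52%. The same formula gives 14% from 1%, 24% from 2% and 85% from 10%. A non-significant test would say little for uncommon complications; the interval shows this directly.

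**The case against.** A good case can be made that little is wrong here.

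- **Descriptive does not forbid an interval.** The analysis plan is not shown and may supply one. The article also says that the estimands for secondary outcomes mirror the primary, which implies a contrast by allocated arm. This weakens the point but does not remove it. The article names the outcomes that get intervals and puts this one in the other list. It expressly defers some other matters to the analysis plan, but not this one.
- **Much of the harm side is already estimated.** Recurrence, (re)admission and unscheduled care can all show harm, and all get effect estimates with intervals where event numbers allow. A reader might infer that benefits are estimated and harms are not; the documents do not support that. The gap is one named outcome.
- **No safety conclusion is planned.** A reader might infer that the trial cannot support a planned conclusion of effectiveness and safety. The Discussion sentence is conditional, it is not a decision rule, and neither the research question nor the objectives claim safety. Nor is it true that the data could not support an estimate: they would allow one at the planned size.
- **Safety is watched in other ways.** Adverse events are followed to day 90, three conditions are always reported as serious, and the monitoring committee sees unblinded data. This protects participants during the trial, but does not itself commit the final report to an estimate.
- **One composite may mislead.** Complications may differ in kind and severity, and a single count of participants with any complication could hide a rare serious excess. This stands, and the remedy has to allow for it.

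It is also true that a reader given counts and denominators could work out the interval. That is a reason why the change is cheap, not a reason to leave it out.

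**Conclusion.** The point holds in a limited form. The article makes a stated choice to treat a listed harm outcome descriptively, gives interval estimates to four other binary secondary outcomes, has no harm objective, and so states neither a between-arm estimate nor a precision for day-14 complications. This does not fit its own emphasis on estimation.

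It is a gap in planned reporting, not an error in a figure, and it does not threaten the primary analysis. Its size depends on the complication risk, which the documents do not give: about ±2 to ±7 points at 225 per arm for assumed risks of 1% to 20%, and slightly wider with loss to follow-up. If the unseen analysis plan already specifies a risk difference with an interval, what remains is the missing objective and the wording in the article.

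**What to change.** 1. **Statistical methods.** Take dexamethasone-related complications out of the purely descriptive list. Report by allocated arm the number and percentage of participants with at least one complication by day 14, and with each type of complication where counts allow, with an unadjusted risk difference and 95% confidence interval (Newcombe, for example) and no hypothesis test. Showing the types guards against a composite that hides differences between them.
2. **Objectives.** Add a secondary objective to estimate the difference between arms in complications by day 14.
3. **Safety wording.** Limit any statement about safety, in the Discussion and in the final report, to the size of excess that the interval excludes.

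The cost is a sentence in the objectives and one in the analysis text or analysis plan. Data collection, sample size and treatment are unchanged. The drawback is a wide interval if events are few; that is honest information about what a trial sized for pain can show.

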### Data collection methods

Data will be collected using electronic Case Report Forms (eCRFs) within a validated REDCap (Research Electronic Data Capture) Academic system provided by the UKCRC-registered Exeter Clinical Trials Unit (ExeCTU). All staff delegated to collect data in this trial will be appropriately trained.

Baseline data will be collected by site staff in person, with the exception of participant-reported outcome questionnaires (EQ-5D-5L and resource use questionnaire) which are self-completed by the participant. Minimum baseline data which must be collected prior to randomisation include eligibility and consent data, baseline pain score, mobile phone number and the minimisation factors (diabetes status, severity of cellulitis, prior antimicrobial therapy for current episode of cellulitis). Remaining baseline data will be collected ideally before randomisation, or after randomisation but prior to administering the first dose of the allocated treatment. This is to allow flexibility for swift recruitment in the emergency setting.

Subsequent pain scores (T1–T6) and PGI-I (T2, T4 and T6) are completed electronically by the participant via SMS, or by site staff directly onto the trial REDCap system if conducting follow-up in person/telephone.

Day 14 and day 90 data are recorded by site staff during follow-up telephone calls. Participants receive an automated SMS to remind them of the appointment, and research staff may try contacting the participant up to three times in order to promote complete follow-up and minimise missing data. If a participant is not engaging with the study at a particular follow-up timepoint, attempts will still be made to contact them at the next timepoint.

PeRSEVERE principles will be followed for participants who cease to engage with the study (see: https://persevereprinciples.org/). Unless a participant expressly indicates that they wish to fully withdraw from the trial, attempts will be made to collect all follow-up data from randomised participants regardless of intervention compliance; if a participant becomes uncontactable and stops engaging with the study, passive data collection will continue where possible and available from the participant’s routine medical notes (e.g., (re)admissions at day 14).

### Potential harms

Adverse events will be reviewed with participants at the day 14 and day 90 follow-up timepoints. All adverse events occurring from randomisation up to 90 days after that are either deemed definitely, probably or possibly related to the intervention (adverse reaction; AR) or meeting the definition of seriousness as detailed below (serious adverse event; SAE) or both (serious adverse reaction; SAR) will be recorded in the study database and monitored by oversight committees.

All SAEs and SARs will be reported to ExeCTU within 24 hours of the site becoming aware for onward reporting to the Sponsor. The trial chief investigator (or delegate) will assess the relatedness of all reported SAE/SARs, and if deemed related, will assess the expectedness using the dexamethasone summary of product characteristics as the reference safety information. If an event is deemed related and unexpected (suspected unexpected serious adverse reaction), the Sponsor will onward report to the Medicines and Healthcare products Regulatory Agency (MHRA) as required.

A serious adverse event is any untoward medical occurrence that:

Results in death.Is life-threatening; an event in which the participant was at risk of death at the time of the event. This does not refer to an event which hypothetically might have caused death if it were more severe.Requires inpatient hospitalisation or prolongation of existing hospitalisation.Results in persistent or significant disability/incapacity.Consists of a congenital anomaly or birth defect.Other ‘important medical events’ may also be considered serious if they jeopardise the participant or require an intervention to prevent one of the above consequences.

The dosage regimen in this trial is a relatively low dose for a short period, meaning the risk of harm is low. In this trial, the following conditions should always be reported as serious adverse events, to ensure adequate monitoring, due to the risk of them occurring as side effects of the study drug in our trial population:

Severe hyperglycaemia (ketoacidosis, hyperglycaemic hyperosmolar state or hyperglycaemia requiring new use of insulin)Gastrointestinal bleeds.Psychosis

The above risks are identified as associated with short-term use of corticosteroids. Further details of how these risks will be managed in the trial can be found in online supplemental file S3.

### Participant timeline

All screening, eligibility, consent and baseline data will be collected in-person during attendance to secondary urgent care. The participant will be asked to complete a short baseline questionnaire pack, and the study team will collect the remaining baseline data (see table 2). Once the minimum baseline data are collected (see data collection section), participants will be randomised and administered the first dose of their allocated intervention. Early follow-up (T1–T6) occurs via SMS survey approximately every 12 hours for the first 3 days, starting at the next available 8 am or 8 pm timepoint after randomisation. This includes the collection of pain scores to calculate the primary outcome plus some minimal data for secondary outcomes. Additional follow-up to collect secondary outcome data via telephone occurs at day 14 (±2 days) and day 90 (±7 days). Participants will be advised to use a paper diary/aide-memoire to record data to help them during the day 14 and day 90 follow-up calls.

**Table 2 T2:** Data collection and schedule of assessments

Assessment/event	Baseline (in person)	Early follow-up (text message survey*)						Late follow-up (telephone)	
	**Recruitment (time 0**)	**T1†**	**T2†**	**T3†**	**T4†**	**T5†**	**T6†**	**14 days** (**±2)‡**	**90** **days** (**±7)‡**
Enrolment**:**									
Eligibility screen	X								
Consent	X								
Demographics	X								
Anthropometry	X								
Contact details	X								
Contact preferences	X								
Comorbidities	X								
Cellulitis details	X								
Risk factors for steroid adverse events	X								
Frailty score (Rockwood),**^31^** if aged 65 or over	X								
Intervention/comparator:									
Randomisation	X								
Study drug dispensed§§	X								
Dexamethasone or placebo dose taken§§	X		X						
Intervention compliance data	X			X^+^					
Assessments:									
Current pain (NRS, 0–10)^+^	X	X	X	X	X	X	X	X	
PGI-I^+^			X		X		X	X	
EQ-5D-5L^+^	X						X	X	X
Analgesia usage	X							X	
Antibiotic usage	X							X	
Complications potentially related to dexamethasone								X	
(Re)admission to hospital								X	
Unscheduled healthcare usage^+^								X	
Health, social care, broader societal resource use^+^	X								X
Recurrence of cellulitis									X
Adverse event review								X	X

+Participant reported*.*

* SMS survey is the default option with options for face-to-face for inpatients or telephone call for outpatients if unable to complete SMS survey.

† The first follow-up text message (T1) will be received at the first available follow-up timepoint (~8 am or ~8 pm) after randomisation, the subsequent five follow-up texts (T2–T6) will be received every 12 hours thereafter*.*

‡ The anchor point (day 0) is the date of randomisation.

§ The first dose of study drug will be given after baseline assessments and randomisation have been performed; the second dose will be taken ~24 hours later (±6 hours).

EQ-5D-5L, EuroQol 5 Dimension 5 Level; NRS, Numerical Rating Scale; PGI-I, Patient Global Impression of Improvement; SMS, short message service.

